### Analytic plan

Primary analyses for Aims 1, 2, and 3 will be conducted using an intent-to-treat approach. Study participants will be retained in their original assignment groups after the randomization in the analysis regardless of the number of missed visits, the use of additional services (e.g., progesterone), or loss to follow-up.
*Aim 1 analysis plan*: comparison of primary and secondary outcomes for GPNC vs. IPNC. To test the hypothesis for aim 1 that women who participated in GPNC will have a lower rate of PTB and other selected birth outcomes as compared to their counterparts in IPNC, multivariate regression models (logistic regression if the outcome is a binary variable and linear regression if the outcome is a continuous variable) will be employed with the intervention assignment as the primary independent variable. We will test the null hypothesis of coefficient of main exposure variable (GPNC vs. IPNC) equals zero. Stratified analyses will be conducted (e.g. race/ethnicity, previous history of PTB) to compare the primary and other outcomes within sub-groups.
*Aim 2 analysis plan*: comparison of racial disparities of primary and secondary outcomes for GPNC vs. IPNC. To test the hypothesis for Aim 2 that the Black-White differences in PTB and other selected birth outcomes is smaller in the GPNC as compared with that in IPNC, we will apply analyses similar to Aim 1 but adding an interaction term of prenatal care (GPNC vs. IPNC) with race (White vs. Black). We will test the null hypothesis of coefficient of interaction term equals zero. For aim 2, only women identified themselves as either Black or White will be included in the primary analysis. Then, we will conduct a sensitivity analysis to see whether including women who self-identified race as “Hispanic ethnicity”, “Mixed race” and “Other race” will influence the primary analysis results. Such sensitivity analysis will be guided by the results from the sub-groups analysis in Aim 1.
*Aim 3 analysis plan*: comparison the effects of GPNC on maternal psychosocial (i.e. activation, engagement, stress) and behavioral (i.e. smoking, healthy eating, healthy practices) changes and exploring whether improving maternal psychosocial and health behavior outcomes will explain the potential benefits of the GPNC on racial disparities in birth outcomes. To address Aim 3, we will first test whether changes in maternal health behaviors or psychosocial factors differ by intervention and race. To do this, a similar analytic plan as used in Aim 1 & 2 will be applied, however, the dependent variables will be changes of health behaviors or psychosocial factors from baseline (~20 weeks) visit to late pregnancy (30–36 weeks). If we observe any significant differences in these health behaviors or psychosocial factors by intervention or race, the next step is to explore whether and to what extent the differences in the intermediate health behavior or psychosocial factors could explain the intervention effect or racial disparities of birth outcomes. To do so, the main multivariate regression models will be examined with and without adjustment for the intermediate health behavior or psychosocial variables.

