### CenteringPregnancy group prenatal care model

The CenteringPregnancy group prenatal care (GPNC) model is distinctly different from the traditional practice of IPNC, requiring a paradigm shift in health care delivery for obstetric healthcare providers and fundamental changes to the patient-provider interaction. In this model, developed and trademarked by the Centering Healthcare Institute (CHI) (Boston, MA), groups of 8–12 women who are all due to deliver in the same month receive their medical care in a series of ten two-hour group sessions which take place through the second and third trimesters [13, 14]. The group sessions begin with patients measuring their own weight and blood pressure, followed by an individual physical assessment from a credentialed health care provider (either a physician or a nurse practitioner/midwife). Once these assessments are complete, the group meets together for structured discussion and activities that follow the curriculum developed by the CHI. Group sessions also include time for socialization, which encourages group members to develop relationships with one another. Group session topics are organized by relevancy to gestational age (Table 1). The model allows the provider to adapt the content according to the needs and priorities of the participants, with deviations from the curriculum noted to be addressed at a later session. Women are encouraged to bring a support person (e.g., boyfriend, husband, friend, family member) for group sessions. CHI has established a site training and annual certification process to assure consistency and quality in implementation for obstetric practices offering GPNC [15]. This model has been implemented in several hundred practices in the U.S. [15].

**Table 1 Tab1:** CenteringPregnancy group prenatal care (GPNC) curriculum outline

1	12–16 weeks	Prenatal testing, nutrition, healthy lifestyle choices	Exercise
2	16–20 weeks	Body changes in pregnancy, common discomforts, oral health	
3	20–24 weeks	Relaxation and stress reduction, breastfeeding	Gestational diabetes
4	24–28 weeks	Family relationships, violence and abuse, family planning, preterm labor	Breastfeeding
5	26–30 weeks	Labor, birth facility	Stress management/relaxation
6	28–32 weeks	The birth experience	
7	30–34 weeks	Newborn care	
8	32–36 weeks	Pregnancy to parenting transition, postpartum emotions, kick counts	Nutrition
9	34–38 weeks	Newborn safety, putting it all together	Preterm labor

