### Patient population

The target population consists of medically low-risk pregnant women of different races/ethnicities. In our retrospective cohort study published in 2012, our study population in the comparison group included 45.8% non-Hispanic White, 25.5% non-Hispanic Black, 22.2% Hispanic and 6.5% “Other” race/ethnicity [21]. We expect that our current study population will be similar.

To be eligible for this study, women will 1) be between 14–45 years of age, and 2) enter prenatal care before their 20^th^ week of gestation. Study exclusion criteria include 1) medical complications of pregnancy which would preclude prenatal care provision by nurse practitioners or participation in group care (e.g. pre-gestational diabetes, severe chronic hypertension, active pulmonary tuberculosis, massive morbid obesity or severe psychiatric illness), 2) multiple gestation, 3) lethal fetal anomalies, and 4) low literacy. The exclusion criteria were set to limit the study participants as low-risk patients, which is consistent with both the GPNC model design and the scope of medical practice of nurse practitioners/nurse midwives who provide GPNC. Women who have participated in this study in a previous pregnancy will also be excluded, in order to maintain independence. Based on our preliminary data, application of these criteria will result in an estimated exclusion of 10% of women for late entry to care and 8% for pre-existing medical complications. The exclusion criteria will be applied to all women before randomization. We will track demographic characteristics and reasons for exclusion for women who are ineligible for the study as well as for those who are eligible but decline participation.

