### Randomization and masking

#### Randomization

Women who are eligible for the study will be offered participation. Women who are interested in participation will have the opportunity to ask questions, confirm interest, provide consent, undergo group assignment, as well as complete the baseline data collection (Survey 1). Women who agree to participate will be randomized 1:1 to IPNC or GPNC based on computer-generated group assignment. These assignments will be stratified by race and ethnicity (Black, White, Hispanic, Mixed, and Other).

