### Interventions

#### GPNC (intervention) group

Women will be grouped with other women who are all due to deliver in the same month, and will receive their routine prenatal care together during ten 2-h group sessions meeting CHI’s established standards for CenteringPregnancy. Women will receive a patient notebook for their health information, educational materials, and activities to promote goal setting and self-care. During the first 30 min of each group session, women will measure and record their own weight and blood pressure, and then a credentialed healthcare provider (nurse practitioner, nurse midwife, or physician) will conduct a brief physical assessment in a semi-private area of the group space. Following the individual health assessments, the healthcare provider and a co-facilitator will lead the group discussion for the remaining 60–90 min of each session. Topics discussed throughout sessions include pregnancy and nutrition, childbirth preparation, exercise, stress management, relationships, and parenting (see Table 1). Women randomized to GPNC will have access to additional IPNC visits (outside of the ten scheduled group sessions) as needed to address complications that may arise between group sessions. The GPNC curriculum is designed to be culturally appropriate and the study site will deliver the intervention in both English and Spanish.

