#### IPNC (control) group

Women will receive standard, traditional individual prenatal care in accordance with the schedule of visits recommended by the American College of Obstetricians and Gynecologists [41]. Women will attend monthly visits for the first 28 weeks of pregnancy, every two to three weeks until 36 weeks gestational age, then weekly until delivery. Visits will include ongoing physical assessment as well as patient education on common complications of pregnancy, childbirth preparation, breastfeeding, and other relevant topics as needed. Women randomized to IPNC will not attend GPNC sessions.

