#### GPNC provision will be monitored additionally through

Perceived Cohesion Scale: This brief, four-question scale measures patients’ sense of belonging and satisfaction with their group;Adherence to GPNC educational curriculum, group size, and continuity: GPNC facilitators and the Project Coordinator currently track curriculum topics covered across sessions, group composition, and measures of GPNC fidelity for at least one session per group. These will be copied as part of data collection for this study;Annual fidelity review results: The OB Center participates in annual fidelity reviews with the Centering Healthcare Institute and has maintained high fidelity to the GPNC model since its first assessment in 2010. Fidelity reviews include a site visit by Centering Healthcare Institute faculty, record reviews, interviews, and observation. The OB Center’s fidelity results will be monitored through the study to assure key elements of the model are in place.

*IPNC provision will be monitored additionally through* medical charts review: IPNC’s educational and counseling topics will be assessed by reviewing medical charts of a randomly selected sample after women have delivered, stratified by provider.

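### GPNC is delivered in shared groups, but the regression models and the sample size treat all women as independent; if outcomes correlate within groups, precision and power are overstated

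*Protocol article*

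**What the plan says.** The Randomization section allocates individuals: "Women who agree to participate will be randomized 1:1 to IPNC or GPNC based on computer-generated group assignment". Care is then organised differently in the two arms. The description of the GPNC model has "groups of 8–12 women who are all due to deliver in the same month receive their medical care" over ten two-hour sessions, and the section on the intervention group repeats the arrangement: "Women will be grouped with other women who are all due to deliver in the same month". For the control arm, "Women randomized to IPNC will not attend GPNC sessions".

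The Analytic plan specifies for Aim 1 "multivariate regression models (logistic regression if the outcome is a binary variable and linear regression if the outcome is a continuous variable", with a test that the coefficient for assignment is zero. Aims 2 and 3 reuse this approach. The Sample size section asks for 1,356 women per arm for Aim 1 and mentions neither an ICC nor a design effect. Independence comes up once, in Patient population, where women who took part in a previous pregnancy are excluded "in order to maintain independence".

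Under GPNC monitoring, facilitators and the coordinator "currently track curriculum topics covered across sessions, group composition, and measures of GPNC fidelity". This information serves process evaluation and does not enter the outcome models.

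**The concern.** This is a partially nested design: individual randomisation, with clustering created by treatment delivery in one arm only. GPNC women share a provider, a co-facilitator, a due month and one another's company. The model description sets time aside for members to form relationships, and the protocol measures group cohesion, so mutual influence is part of the intended mechanism.

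If outcomes are positively correlated within groups, the GPNC arm carries less information than its head count suggests. Ordinary logistic or linear regression then gives confidence intervals that are too narrow and p-values that are too small, and the planned power is overstated. The same models serve Aim 3, where a significant psychosocial or behavioural difference is what triggers the explanatory step of adding intermediates to the main models.

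**Working it through.** **Inputs from the protocol.** IPNC preterm birth rate 13%; relative risk 0.70, so 9.1% under GPNC; alpha 0.05, taken as two-sided (sidedness is not stated, but the null is a zero coefficient); power 90%; 1,356 per arm; 15% attrition; target 1,580 per arm; groups of 8-12.

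**Assumptions, not in the protocol.** ICC 0.01-0.05; m = 4, 10 or 12 trial women per GPNC group.

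**Step 1: the plan's own figure.** Two proportions, pooled variance, no continuity correction, independent women:

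n = [1.960 × √(2 × 0.1105 × 0.8895) + 1.2816 × √(0.13 × 0.87 + 0.091 × 0.909)]² / 0.039² = (0.8690 + 0.5671)² / 0.001521 = 1,355.9.

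This rounds up to the stated 1,356, so the figure contains no clustering allowance.

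**Step 2: evaluable women.** 1,580 × 0.85 = 1,343 per arm. The formula of Step 1 then gives 89.7% power before any clustering. The 0.3 points below 90% come from the attrition allowance, not from clustering.

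**Step 3: clustering in the GPNC arm only.** DE = 1 + (m − 1) × ICC multiplies the GPNC-arm variance; the IPNC arm keeps a factor of 1. Power of a correctly adjusted 5% test is

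Φ{[0.039 − 1.960 × √(0.1105 × 0.8895 × (1 + DE)/1,343)] / √[(0.1131 + DE × 0.0827)/1,343]}.

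Example, m = 10 and ICC 0.05: DE = 1.45; the critical difference is 0.02625, the standard error under the alternative is 0.01317, and Φ(0.968) = 83.4%.

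**Step 4: the unadjusted test.** When group effects vary but average to zero, the true standard error of the contrast is √((1 + DE)/2) times the one used. Type I error is therefore 2 × [1 − Φ(1.960/√((1 + DE)/2))].

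| Trial women per group | ICC | DE | Power, 1,343 per arm | Type I error, unadjusted |
|---|---|---|---|---|
| 4 | 0.01 | 1.03 | 89.3% | 5.2% |
| 4 | 0.05 | 1.15 | 87.6% | 5.9% |
| 10 | 0.01 | 1.09 | 88.5% | 5.5% |
| 10 | 0.05 | 1.45 | 83.4% | 7.7% |
| 12 | 0.01 | 1.11 | 88.2% | 5.6% |
| 12 | 0.05 | 1.55 | 81.9% | 8.3% |

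Against the 89.7% baseline, clustering costs 0.4-2.1 points with 4 women per group, 1.2-6.3 with 10, and 1.5-7.8 with 12.

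**The case against.** The strongest reply is that the harm is conditional. No ICC is given for preterm birth or for any scale, and a positive one is an inference from how care is delivered. A reader might conclude that the GPNC standard errors are certainly too small; the protocol supports only that they are if outcomes correlate within groups. This stands, and the point is worded accordingly.

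A reader might also take the type I figures to apply under any null. They do not. Women are randomised individually and groups form afterwards. If GPNC changed no woman's outcome, forming groups later could not invalidate the individual comparison, and correlation due only to a shared due month would not inflate the error rate. The figures apply when group effects differ but average to zero.

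Cluster size is uncertain too. What counts is trial women with outcomes per group. Fifteen per cent attrition turns 10 into 8.5. The practice has run groups since 2008 and expects about half of eligible women to enrol, so non-trial patients may share the groups. Women who miss sessions stay in their arm under intention to treat, which weakens any correlation. On the other side, 180 eligible women a month at 50% recruitment and 1:1 allocation give about 45 GPNC women monthly, enough for four groups of 10. The protocol does not settle this, hence the range from 4 to 12.

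Finally, the article is condensed, and an analysis plan not shown could add a robust variance to the named models. That would repair the standard errors. It does not reach the sample size, which is stated in full and assumes independence.

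**Conclusion.** The point holds in conditional form. The design is partially nested, the named models ignore it, and 1,356 per arm allows nothing for it. For preterm birth the consequence is probably modest: over the assumed ICC range of 0.01-0.05, Aim 1 power lies between 89.3% and 81.9%, depending on whether 4 or 12 trial women share a group, against 89.7% without clustering. Type I error of the unadjusted test lies between 5.2% and 8.3%, under the zero-mean condition above. The direction follows from the design once the ICC is positive; the size rests wholly on assumed values.

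The effect may be larger for the Aim 3 psychosocial outcomes, where members can influence one another directly. A reader might want to attach a higher ICC, such as 0.10, to those scales; nothing in the protocol supports a particular value, so none is used. Nor do these figures show that the trial is too small to proceed.

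**What to change.** 1. Record for every woman randomised to GPNC the group to which she was first assigned, and keep that as her cluster whatever she attends, in line with intention to treat. Group composition is already tracked, but the participant-level care data listed in the process evaluation include visit type and provider, not a group identifier. Linking each woman to a group, never-attenders included, is a small added task.
2. Analyse Aims 1-3 either with a random intercept for group in the GPNC arm only, or with cluster-robust standard errors in which each IPNC woman is her own cluster. Name one of these as primary. The robust option leaves the estimated odds ratio from the planned logistic model unchanged, and with up to 12 women per group there would be at least about 1,580/12 = 132 groups to support it.
3. Restate Aim 1 power over a range of ICC and of trial women per group, as in the table. No additional enrolment is proposed.

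The cost is one linked identifier, a few sentences of analysis wording, slightly wider confidence intervals and a slightly lower stated power.

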### Specific aims and hypotheses

The proposed study will employ a RCT design adequately powered to detect difference in PTB by intervention and race. The study will be conducted in a large prenatal care provider in South Carolina (SC), with historically high PTB rates of 16.4%. The proposed study builds on an established research program focused on assessing the impact of GPNC vs. IPNC on birth outcomes and will investigate the following Specific Aims:

### Specific Aim 1

To compare the rate of PTB prior to 37 weeks gestational age and other selected birth outcomes and pregnancy complications (e.g. birth weight, caesarean section rate) among women who participate in CenteringPregnancy GPNC to their counterparts in IPNC.

#### Study hypothesis 1

Women who participate in GPNC will have a lower rate of PTB and other improved birth outcomes as compared to their counterparts in IPNC.

### Specific Aim 2

To compare the risk difference of PTB and other selected birth outcomes of Black women vs. White women in GPNC to the risk differences of Black women vs. White women in IPNC.

#### Study hypothesis 2

The risk difference of PTB and other selected birth outcomes between Black and White women in the GPNC group is smaller than that in the IPNC group.

### Specific Aim 3

To compare whether women in the GPNC have improved maternal psychosocial (i.e. activation, engagement, stress) and behavioral (i.e. smoking, healthy eating, health practices) outcomes as compared to their counterparts in IPNC and to explore whether improving certain maternal psychosocial and behavioral outcomes will explain the potential benefits of GPNC on racial disparities in birth outcomes.

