### Sample size

We calculated our sample size based on Aims 1 & 2 with the primary outcome of PTB. Based on the literature and our preliminary data, the rate of PTB was approximately 10-16% of women in the traditional care setting [16]. The odds ratio of comparing PTB in GPNC to IPNC was 0.67 in the Ickovics study and 0.53 in our own study [16, 17]. Our own work also suggests that the risk difference of having PTB between Black women and White women was 1.0% in the IPNC and 2.4% in the GPNC. Taken together, it is reasonable to assume that the relative risk of PTB in the IPNC group could range from 10% to 16%. For aim 1, assuming the proportion of PTB rate of 13%, our study will need *N* = 2,712 (1,356 in each group) to detect the relative risk of PTB in GPBC vs. IPNC of 0.70 with an alpha of 0.05 and a power of 90%. For aim 2, assuming the proportion of PTB rate of 0.02, our study will need *N* = 2,748 (1,374 in each group) to detect reduction in risk difference of 1.4% between Black and White women in GPNC vs. IPNC group with an alpha of 0.05 and a power of 90%. With an estimated 15% attrition rate, we will target recruiting 3,160 (*N* = 1,580 in each group) women for this study. Table 3 gives the estimated minimum number (in each group) required to achieve an alpha of 0.05 and a power of 80% or 90% to detect the risk ratio from 0.5 to 0.7 in Aim 1 and to detect the risk difference from 0.01 to 0.08, given the rate difference (P_0_) of preterm birth between Black women and White women at the IPNC group ranges from 2% to 3% in Aim 2, This sample size estimates that the proposed study will have 90% power to detect racial difference on PTB for Aim 2.

**Table 3 Tab3:** Sample size and power calculations

	Power = 80%			Power = 90%		
Aim 1	RR = 0.50	RR = 0.60	RR = 0.70	RR = 0.50	RR = 0.60	RR = 0.70
P_0_ = 0.10	435	721	1,356	582	965	1,814
P_0_ = 0.13	326	540	1,014	436	723	1,356
P_0_ = 0.16	258	427	800	345	571	1,070
Aim 2	RD = 0.01	RD = 0.014	RD = 0.018	RD = 0.01	RD = 0.014	RD = 0.018
P_0_ = 0.02	2,319	1,027	526	3,103	1,374	704
P_0_ = 0.03	3,826	1,799	995	5,121	2,048	1,332
P_0:_ the RD of PTB in IPNC group; RR: relative risk						

Abbreviation: RD = risk difference

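### For preterm birth and other binary outcomes, Aim 2 asks whether the Black-White risk difference shrinks, but the planned test is of a logistic interaction, which has a different null

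*Protocol article*

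**What the plan says.** The additive scale appears in three places in the protocol article.

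- Specific Aim 2: "To compare the risk difference of PTB and other selected birth outcomes of Black women vs. White women in GPNC" with the same quantity in IPNC.
- Study hypothesis 2: the risk difference "between Black and White women in the GPNC group is smaller than that in the IPNC group".
- Sample size: Aim 2 is planned "to detect reduction in risk difference of 1.4% between Black and White women in GPNC vs. IPNC group". The Table 3 footnote defines P0 as the risk difference in the IPNC group.

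The analysis is on another scale. For Aim 1 the Analytic plan names "logistic regression if the outcome is a binary variable" and linear regression for continuous outcomes. For Aim 2 it repeats the Aim 1 analyses, "adding an interaction term of prenatal care (GPNC vs. IPNC) with race (White vs. Black"). The decision rule follows: "We will test the null hypothesis of coefficient of interaction term equals zero". Preterm birth, the primary outcome, is binary. The article names no identity-link model, standardised risk difference or other additive contrast for Aim 2.

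**The concern.** In a logistic model with arm, race and their product, the product coefficient is the log of the Black-White odds ratio in GPNC divided by the Black-White odds ratio in IPNC. Hypothesis 2 concerns the Black-White risk difference in GPNC minus that in IPNC. When two groups start at different risks and an intervention moves both, these quantities cannot in general be zero together. Aim 1 expects such a movement (relative risk 0.70), so the discrepancy arises under the trial's own expectations.

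Reducing the racial disparity is one of the trial's two headline questions. If group care lowers the odds of preterm birth by the same factor in both races, the disparity as the protocol defines it narrows. The named test is then under its exact null, and has no more than its type I error rate of detecting the narrowing at any sample size. This is not a detail left to an unseen analysis plan: the article itself commits to a model and a null hypothesis that do not match its stated hypothesis.

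**Working it through.** **The plan's own figure.** Aim 2 uses P0 = 0.02, a reduction of 0.014, alpha 0.05 and 90% power. The two-proportion formula, two-sided with pooled variance under the null, takes p1 = 0.02, p2 = 0.006 and mean 0.013:

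n = [1.960·√(2·0.013·0.987) + 1.2816·√(0.02·0.98 + 0.006·0.994)]² / 0.014² = (0.3140 + 0.2049)² / 0.000196 ≈ 1,374 per group.

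This reproduces the protocol. It does so by treating two risk differences as if they were two single-group proportions, so the 90% describes neither interaction test.

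**Inputs for the scale check.**

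- IPNC preterm birth 13% and relative risk 0.70, hence 9.1% in GPNC (Sample size).
- Prior odds ratios 0.67 and 0.53 (Sample size).
- Gap 2.4 points in IPNC and 1.0 in GPNC, as given under Preliminary research. The Sample size section prints these two the other way round; the Preliminary research orientation is used here.
- Race mix 45.8% White and 25.5% Black (Patient population), so White share 45.8/71.3 = 0.642 among Black and White women.
- Race-specific risks are not in the protocol and are assumed. Three IPNC baselines are used (White / Black): 12.0% / 14.4%; 12.14% / 14.54%, which gives 13% overall with a 2.4-point gap at the 64:36 mix; and a wider-gap 10% / 16%.

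**Formulas.** Contrast on the stated scale: (B − W in GPNC) − (B − W in IPNC). Planned test: ROR = [odds(B)/odds(W) in GPNC] / [odds(B)/odds(W) in IPNC].

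First row in full: IPNC odds are 0.13636 and 0.16822. Multiplying each by 0.67 and converting back gives 8.37% and 10.13%. The gap is 1.76 points and the ROR is 1.

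| IPNC W / B (%) | Scenario | GPNC W / B (%) | Gap (points) | ROR |
|---|---|---|---|---|
| 12.0 / 14.4 | common OR 0.67 | 8.37 / 10.13 | 2.40 → 1.76 | 1.000 |
| 12.0 / 14.4 | common OR 0.53 | 6.74 / 8.19 | 2.40 → 1.45 | 1.000 |
| 12.0 / 14.4 | gap unchanged | 8.40 / 10.80 | 2.40 → 2.40 | 1.070 |
| 12.14 / 14.54 | gap slightly narrower | 8.38 / 10.38 | 2.40 → 2.00 | 1.028 |
| 12.14 / 14.54 | planning case | 8.74 / 9.74 | 2.40 → 1.00 | 0.915 |
| 10 / 16 | common OR 0.67 | 6.93 / 11.32 | 6.00 → 4.39 | 1.000 |
| 10 / 16 | common OR 0.53 | 5.56 / 9.17 | 6.00 → 3.61 | 1.000 |
| 10 / 16 | gap unchanged | 6.10 / 12.10 | 6.00 → 6.00 | 1.236 |

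The unchanged-gap ROR in row 3 is [(0.108/0.892)/(0.084/0.916)] / 1.2336 = 1.070.

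**Size against sampling error.** Take 1,374 Black and White women per arm at 64:36, about 883 White and 491 Black.

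- Risk-difference scale, SE = √Σ p(1−p)/n over the four cells. In the planning case this is 2.54 points; 1.4/2.54 = 0.55, so power is about 9%.
- Logistic scale, SE = √Σ 1/[n·p(1−p)] = 0.254. Log 0.915 = −0.089, ratio 0.35, so power is about 6%.
- If 1,374 counts women of every race, about 71% are Black or White, and the figures fall to about 8% and 6%.

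**The case against.** The best counter-argument is that the scale is not what limits Aim 2. In the planning case both scales point the same way. Where they part, the log ROR at the protocol-based baselines is between 0 and 0.08, against a standard error of about 0.25. In the common-OR 0.67 case, the risk-difference test has power of about 6%, against 5% for the logistic test under its exact null, so either would usually be reported as no effect. For 90% power in the planning case, the additive contrast would need about 47,400 Black and White women per arm and the logistic interaction about 118,000. All of this stands. Low power is the larger practical problem.

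It is also true that an unadjusted model with arm, race and their product is saturated, so the four risks and the additive contrast can be recovered from it. Race-stratified analyses are planned as well. That makes the remedy easy; it does not change which coefficient the plan tests. For continuous outcomes the linear interaction is already a difference of differences, and nothing needs changing.

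A reader might infer more than the documents support:

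- *That an unchanged gap would be reported as a worsening disparity.* An ROR of 1.07 is 0.068 on the log scale; with SE about 0.25, z is about 0.27 and p about 0.79. That is a null result with a point estimate slightly above 1.
- *That the test could readily favour group care when Hypothesis 2 is false.* In the worked cases this arises when group care raises preterm birth, contrary to the planned effect. For example, risks moving from 12.0% / 14.4% to 16.0% / 18.6% widen the gap from 2.4 to 2.6 points with an ROR of about 0.97.
- *That Aim 1 has the same fault because it was planned on a relative risk.* For a two-arm comparison, no effect is the same null on the odds-ratio, risk-ratio and risk-difference scales.

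**Conclusion.** The mismatch is real and follows from the wording of the Specific aims, Sample size and Analytic plan sections. It does not depend on any assumed rate. For preterm birth and other binary outcomes, the plan tests a multiplicative interaction while its hypothesis is a difference in risk differences.

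Under a common odds ratio equal to either cited prior value, the gap narrows by 27% (0.64 of 2.40 points) or 40% (0.95 of 2.40 points), and the planned coefficient is exactly zero. These magnitudes rest on assumed race-specific risks, but the exact zero holds at every baseline tried. The consequence is a test aimed at the wrong null, not a demonstrated false claim of harm or benefit at the planned size. Nor does correcting the scale rescue Aim 2: power in the planning case stays at about 9%, against the stated 90%.

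**What to change.** For binary outcomes, define the primary Aim 2 contrast as (Black − White risk in GPNC) minus (Black − White risk in IPNC), and test that contrast against zero. Two routes are suitable:

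- an identity-link or linear-probability model with robust standard errors; or
- standardised risks from the logistic model already planned, with a delta-method or bootstrap interval.

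Keep the ratio of odds ratios as a secondary result, labelled as multiplicative interaction. Leave the linear-model interaction for continuous outcomes as it is.

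The cost is a change to the analysis wording and a few lines of code, with no new data, and it should be settled before results by arm are seen. The revised text should also say that the change does not provide 90% power for Aim 2, so the interval for the contrast will be wide: at an SE of about 2.5 points, roughly ±5 points (1.96 × 2.5).
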